## Abstract

**Background:**

Acupuncture has long been used to treat chronic stable angina pectoris (CSAP), but the acupuncture prescription for CSAP varies. This trial will compare the therapeutic effects between the acupoints on the Heart Meridian and the acupoints on the Lung Meridian for treating CSAP, so as to provide a better prescription for acupuncture treatment of CSAP.

**Methods:**

This is a multicenter randomized controlled trial. A total of 148 CSAP patients will be randomly allocated into two groups through central randomization in a 1:1 ratio. This trial will include a 2-week screening period, a 4-week treatment period, and a 4-week follow-up period. The primary outcome is the frequency of angina attacks from baseline to 4 weeks after inclusion. Secondary outcomes include the frequency of angina attacks from baseline to 4 weeks after acupuncture treatment, the pain intensity of angina, total ischemia burden, heart rate variability, QT dispersion, the score of Seattle Angina Questionnaire, and the score of Short-Form of McGill Pain Questionnaire. These outcome measures will be evaluated at baseline, at the end of acupuncture treatment, and at the end of follow-up.

**Discussion:**

We hypothesize that the effectiveness of puncturing at acupoints on the Heart Meridian will not be the same as those on the Lung Meridian. The results will provide further evidence of Meridian-Viscera Association theory and references for acupoints selection in the clinical practice.

**Trial registration:**

Chinese Clinical Trial Registry ChiCTR1900025804. Registered on September 9, 2019

## Background

Chronic stable angina pectoris (CSAP) is a common manifestation of coronary artery disease (CAD) and serves as the initial symptom in approximately half of all patients with CAD [1–4]. In America, an estimated 15.5 million adults have chronic CAD, and more than 7 million adults suffer from angina [5]. CSAP is associated with an increased risk of major cardiovascular events and sudden cardiac death [6], significantly impacts the patients’ quality of life (Qol) [7], and increases the considerable healthcare expenditure [8]. Currently, the main management of CSAP is pharmacological treatment including β-blockers, angiotensin-converting enzyme inhibitors (ACEI), angiotensin II receptor blockers (ARB), and antiplatelet medications and statins [9]. However, the efficacy of medications is not satisfactory for the ignored side effects [2].

Acupuncture has been used for cardiovascular disorders including precordial pain and palpitation for thousands of years [10, 11]. The therapeutic effects of acupuncture for treating CSAP are gradually being accepted in Western counties. Recently, some randomized controlled trials (RCT) had investigated the clinic value of acupuncture for treating CSAP. For example, acupuncture as an adjunctive treatment to antianginal therapy could significantly alleviate angina compared to the waiting list [12]; acupuncture increased cardiac work capacity significantly compared to sham acupuncture, which expressed as dPRP (difference in pressure-rate-product between rest and maximum exercise) and maximal PRP during exercise [13]; and acupuncture was superior to isosorbide dinitrate and nifedipine in improving the symptoms of coronary angina pectoris [14]. Since these studies proved the efficacy of acupuncture for CSAP from different aspects, how to improve the effectiveness and accessibility of acupuncture for CSAP attracts increasing attention.

According to the traditional Chinese acupuncture theory, meridians and viscera are closely related in physiological function, mutually affected in pathological changes and treatment. The Heart Meridian connects with the heart directly, and the Lung Meridian indirectly associates with the heart. Both of these two meridians can be used for cardiovascular diseases in clinical practice [15, 16]. Based on the theory of Meridian-Viscera Association, our previous study found that not only the acupoints on the Heart Meridian and Pericardium Meridian, but also the acupoints on the Lung Meridian could improve the symptoms and the Qol of CSAP patients. To further optimize the acupoint prescription and provide more convenience and simple acupuncture therapy for CSAP, we designed this RCT. In this study, acupuncture prescription is composed of the basic acupoints (local acupoints close to the heart) and additional acupoints (acupoints on the Heart Meridian or the Lung Meridian), which are far from the heart. The aim of this study focuses on providing the reference for acupoint and acupuncture modality selection in acupuncture treating CSAP, so as to promote the application of acupuncture for treating CSAP. The intradermal needle has been selected as the acupuncture intervention for its advantages including continuous stimulation, high convenience, high safety, and non-invasiveness compared with the filiform needle [17, 18].

## Methods and design

### Study design

This is a two-arm, double-center, randomized controlled trial. A total of 148 CSAP patients will be enrolled and randomly assigned to two groups through central randomization in a 1:1 ratio. This trial will include a 2-week screening period, a 4-week treatment period, and a 4-week follow-up period. Outcome assessments will be performed at the baseline, the end of treatment, and the end of follow-up (see Fig. 1 for the details of the study schedule).

**Fig. 1 Fig1:**
[figure not shown]
Flowchart of the study design

The reporting of this trial is conducted according to the Standard Protocol Items: Recommendations for Intervention Trials (SPIRIT) guidelines [19] (Fig. 2). The Consolidated Standards of Reporting Trials (CONSORT) and the Standards for Reporting Interventions in Clinical Trials of Acupuncture (STRICTA) have been used as frameworks of methodology for the design of this protocol [20].

**Fig. 2 Fig2:**
[figure not shown]
Standard Protocol Items: Recommendations for Interventional Trials (SPIRIT) schedule. VAS, visual analog scale; TIB, total ischemia burden; HRV, heart rate variability; QTd, QT dispersion; SAQ, score of Seattle Angina Questionnaire; SF-MPQ, Short-Form of McGill Pain Questionnaire; SAS, self-rating anxiety scale; SDS, self-rating depression scale

### Participants

The CSAP patients will be recruited from two clinical centers, including the Hospital of Chengdu University of Traditional Chinese Medicine (CDUTCM) and the First Affiliated Hospital of Zhejiang Chinese Medical University (ZCMU).

All CSAP patients will undergo a careful physical examination including electrocardiogram (ECG), echocardiographic tissue Doppler imaging (TDI), blood pressure test, blood sugar test, routine test (blood, urine, and stool), biochemical blood test (ALT, AST, BUN, Scr), myocardial zymogram test (LDH, α-HBDH, CK, CKMB), serum immunoglobulin E (IgE), myoglobin (Myo), and cardiac troponin l (cTnl) before inclusion.

### Recruitment strategy

Participants will be recruited from the outpatient and inpatient departments of Cardiology in the Hospital of CDUTCM and the First Affiliated Hospital of ZCMU from October 2019 to August 2021.

The recruitment strategies include advertisements in the post, leaflets, the website of CDUTCM (http://cdutcm.edu.cn/), and ZCMU (https://www.zcmu.edu.cn/).

### Diagnostic criteria

The diagnostic criterion bases on the Guideline for Diagnosis and Treatment of stable coronary artery disease (SCAD) issued by Chinese Society of Cardiology, Chinese Medical Doctor Association of Cardiovascular Physicians and Editorial Committee of Chinese Journal of Cardiology in 2018 [21].

### Inclusion criteria

The patients will be included if they meet the following 6 items: (1) match the diagnostic criteria of SCAD; (2) meet the criteria of Class I or Class II according to the Canadian Cardiovascular Society (CCS) angina pectoris severity grade [22]; (3) age from 45 to 70 years; (4) have experienced angina attack in the last 3 months, and the attack frequency ≥ twice a week in the most recent month; (5) have a standardized medication history at least 2 months before enrolment (sustaining the same medication, usage, and dose), the basic therapeutic medication retains to one or more of the following: β-blockers ACEI, ARB, and antiplatelet medications and statins; and (6) have signed the informed consent.

### Exclusion criteria

The patients will be excluded if they match the following 9 items: (1) be accompanied with acute myocardial infarction, severe arrhythmia (advanced atrioventricular block, ventricular tachycardia, supraventricular tachycardia, frequent premature beats); (2) be accompanied with severe psychiatric illness; (3) fail to control hypertension (systolic blood pressure ≥ 140 mmHg and/or diastolic blood pressure ≥ 90 mmHg) or diabetes mellitus (HbA1 above 7% in last 3 months); (4) have severe digestive, urinary, respiratory, hematological, nervous, or endocrine system diseases; (5) be pregnant or during lactation or intending to be pregnant in the 6 months; (6) have received acupuncture therapy due to cardiovascular illness in the last 1 month; (7) have the bleeding tendency and dermatitis; (8) be in the allergic constitution and be allergic to adhesive tape; or (9) be participating in any other clinical trials.

### Sample size

In this study, we assume that H0 represents the clinical effect of Group A is the same as Group B; H1 represents the effect of Group A is not the same as Group B.

According to the formula: $$ n=\frac{2{\sigma}^2}{{\left(\mu 1-\mu 2\right)}^2}\times {\left({\mu}_{\alpha /2}+{\mu}_{\beta}\right)}^2 $$ [23]. In this study, assuming α = 0.05 (both sides), 1-β = 0.80. Based on our previous study [12], *μ*1 is the improvement of the frequency of angina attacks in the acupoints on the disease-affected meridian group, and *μ*2 is the improvement of the frequency of angina attacks in the acupoints on the non-affected meridian group. With *μ*1 = 5.57 and *μ*2 = 3.14, σ is estimated to be 5, and the sample size is calculated as 67 per group. Considering a dropout rate of 10%, we concluded that the sample size is 73.6 per group, and each group needs 74 cases after taking an integer. Therefore, a total of 148 CSAP patients will be finally recruited.

### Randomization

To guarantee randomization concealment adequately, and not be influenced either by the acupuncturists or the participants, randomization will be performed by a clinical information management system (Beijing Bioknow Information Science & Technology Co. Ltd., China). The investigators are trained to apply for randomization through text messages, online websites, or telephone application. When randomization information (including the participants’ name, gender, and date of birth) is sent to the randomization center, the random numbers and group assignment will immediately be delivered to the acupuncturists.

### Blinding

It is difficult to blind acupuncturists in acupuncture clinical trials. However, it is feasible to conceal the patients and group assignments from outcome assessors and statistical analysts. Patients are told that they will receive one of 2 effective acupuncture interventions after enrollment, and during the acupuncture treatment, patients in different groups will be in separate compartments to avoid communication. Outcome assessors and statisticians will be blind to the group allocations.

### Intervention

All patients in the two groups will receive a total of 7–9 acupuncture sessions (at least 7 sessions) during 4 weeks. By intradermal needle, acupuncture stimulation will last for 48–72 h in each session with a 1-day interval between each session.

The acupoint prescription will be composed of the basic acupoints and additional acupoints. The basic acupoints include bilateral *Xinshu* (BL15) and *Juque* (CV14), which are close to the heart. The basic acupoints will be used for the patients in both groups. The additional acupoints are all on the forearm, which are far from the heart relatively. For group A, 3 additional acupoints on the Heart Meridian will be selected, including bilateral *Shenmen* (HT7), *Yinxi* (HT6), and *Tongli* (HT5). For group B, 3 additional acupoints on the Lung Meridian will be selected, including bilateral *Taiyuan* (LU9), *Lieque* (LU7), and *Kongzui* (LU6) (Fig. 3).

**Fig. 3 Fig3:**
[figure not shown]
Locations of Acupoints. CV14 (*Juque*), on the anterior meridian line of the upper abdomen,6 cun above the navel. BL15 (*Xinshu*), on the back,1.5 cun on the lateral to the lower border of the spinous process of the 5th thoracic vertebra. HT7 (*Shenmen*), on the wrist, at the ulnar end of the transverse crease of the wrist, in the depression on the radial side of the tendon of the flexor carpi ulnaris. HT6 (*Yinxi*), on the palmar side of the forearm, the point is on the radial side of the tendon of the flexor carpi ulnaris,0.5 cun above the transverse crease of the wrist. HT5 (*Tongli*), on the palmar side of the forearm, the point is on the radial side of the tendon of the flexor carpi ulnaris,1 cun above the transverse crease of the wrist. LU9 (*Taiyuan*), on the radial side of the transverse crease of the wrist, where the radial artery pulsates. LU7 (*Lieque*), on the radial margin of the forearm,1.5 cun above the transverse crease of the wrist, between the brachioradial muscle tendon and the long abductor muscle tendon of thumb. LU6 (*Kongzui*), on the radial palmar side of the forearm, on the line connecting *Chize* (LU5) with *Taiyuan* (LU9),7 cun above the transverse crease of the wrist.

The intradermal needle (0.2 mm in diameter and 1.5 mm in length or 0.2 mm in diameter and 1.2 mm in length, Seirin Pyonex®; Seirin Corporation, Shizuoka, Japan) will be inserted and retained in each acupoint for 48–72 h (at least retained for 48 h). During the retaining period of the intradermal needle, patients will be requested to press the needle perpendicularly for 3 to 4 times every 24 h, and each time lasts for around 30 s. The manipulation will be performed according to the National Standard of the People’s Republic of China “Standardized Manipulations of Acupuncture and Moxibustion-part 8: Intradermal needle” (GB/T 21709.8-2008) [24].

### Basic treatment

The basic treatment for CSAP includes health education and primary medications, which will be performed from the baseline to the end of the follow-up period. Health education with CSAP aims to help the patients understand and master the basic knowledge of CSAP, such as risk factors, diagnosis, prevention, daily medication, and emergency treatment methods. Basic medications include β-blockers, ACEI, ARB, and antiplatelet medications and statins. Patients can choose one or several of the four medications as maintenance therapy according to cardiologists’ advice.

### Outcomes

#### Primary outcome

In this trial, the primary outcome is the frequency of angina attacks from baseline to 4 weeks after inclusion. The frequency of angina attacks will be recorded in the angina diary. The angina diary will be requested to complete and return to assessors in time by paper diary, emails, short messages, or telephone calls throughout the whole 10 weeks observation period.

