#### Secondary outcomes

The secondary outcomes include: (1) the frequency of angina attacks from baseline to 4 weeks after the acupuncture treatment, (2) the pain intensity of angina which is assessed by visual analog scale (VAS), (3) total ischemia burden (TIB) and heart rate variability (HRV) which are recorded by 24-h dynamic electrocardiogram (DCG), (4) QT dispersion (QTd) which is recorded by ECG, (5) the score of Seattle Angina Questionnaire (SAQ), (6) the score of Short-Form of McGill Pain Questionnaire (SF-MPQ), (7) the score of self-rating anxiety scale (SAS), (8) the score of self-rating depression scale (SDS), and (9) the expectation values of acupuncture treatment which is composed of 7 questions and designed by our team. The VAS score will be extracted from the angina diaries. The second to eighth secondary outcomes will be evaluated at baseline, at the end of acupuncture treatment and at the end of follow-up. Moreover, the expectation of acupuncture treatment in each patient will be evaluated at baseline.

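### The primary outcome can be read as a change or as an unadjusted 4-week frequency, and the SD of 5 and 80% power are tied only to the change

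*Protocol article*

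**What the plan says.** - **Outcome definition** (Primary outcome; similar wording in the Abstract and under Data analysis): "the primary outcome is the frequency of angina attacks from baseline to 4 weeks after inclusion". The article does not say whether this is the frequency over the four weeks or the change from baseline.
- **Sizing** (Sample size): μ1 "is the improvement of the frequency of angina attacks in the acupoints on the disease-affected meridian group", and μ2 is the same quantity in the other group. The values are 5.57 and 3.14, and "σ is estimated to be 5, and the sample size is calculated as 67 per group". No time unit or counting window is attached to any of these figures.
- **Model** (Data analysis): ANCOVA of the frequency if it is approximately normal, with age, sex, disease duration and site as covariates. Baseline attack frequency is not in the list.
- **Timing** (Study design): "This trial will include a 2-week screening period, a 4-week treatment period, and a 4-week follow-up period". The Primary outcome section has the angina diary kept for 10 weeks in all. No section names the baseline window for attack frequency.
- **First secondary outcome** (Secondary outcomes): "the frequency of angina attacks from baseline to 4 weeks after the acupuncture treatment".

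**The concern.** Three sections each describe the primary variable, and together they do not fix one. The sample size section describes a change. The outcome definition and the model, read literally, describe a frequency after baseline, analysed without the baseline value. These two variables generally have different standard deviations, and the SD drives the sample size. The 80% power is therefore shown for only one of the two analyses that the text allows.

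The first secondary outcome uses the same form of words. Read as a cumulative window, it runs from baseline to the end of follow-up and so contains the whole primary window. A result on it would then partly repeat the primary result and could not be taken as evidence that the effect lasts.

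**Working it through.** **Inputs.** From Sample size: "assuming α = 0.05 (both sides), 1-β = 0.80"; means 5.57 and 3.14; SD 5; 67 per group. The correlation r between a patient's baseline and 4-week frequency is not given, so it is varied from 0.3 to 0.8.

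**Step 1. The plan's own figure.** Difference = 5.57 − 3.14 = 2.43.

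n = 2 × 5² / 2.43² × (1.96 + 0.84)² = 66.46 (unrounded normal quantiles), so 67 per group. Power at 67 is 80.3% by the normal approximation. For dropout, 67 × 1.1 = 73.7 (the article prints 73.6), which rounds up to 74 per group and 148 in total. The arithmetic is sound for a difference in improvement.

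**Step 2. Does the difference carry over?** Randomisation makes the expected baseline equal in the two arms. The expected between-group difference in improvement is then the same size as that in the 4-week frequency, provided both use one unit. So 2.43 stands under either reading. Changing the unit of difference and SD together also leaves n at 67 (for example 2.43/2 with 5/2), so the missing unit does not by itself alter the sample size.

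**Step 3. Does the SD carry over?** Assume that SD 5 is the SD of change and that the variance is the same at baseline and at 4 weeks. Then:

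- SD of change = s × √(2(1 − r)) = 5, so the SD of the 4-week frequency is s = 5 / √(2(1 − r)).
- Residual SD with baseline as covariate = s × √(1 − r²) = 5 × √((1 + r)/2).
- Power at 67 per group = Φ(2.43 / (SD × √(2/67)) − 1.96).

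| r | SD, 4-week frequency, no baseline | n per group | Power at 67 | Residual SD, baseline as covariate | n per group | Power at 67 |
|---|---|---|---|---|---|---|
| 0.3 | 4.23 | 48 | 91% | 4.03 | 44 | 94% |
| 0.4 | 4.56 | 56 | 87% | 4.18 | 47 | 92% |
| 0.5 | 5.00 | 67 | 80% | 4.33 | 50 | 90% |
| 0.6 | 5.59 | 84 | 71% | 4.47 | 54 | 88% |
| 0.7 | 6.45 | 111 | 59% | 4.61 | 57 | 86% |
| 0.8 | 7.91 | 167 | 43% | 4.74 | 60 | 84% |

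Without baseline, power is above plan for r below 0.5, equal to plan at 0.5 and below plan for r above 0.5. With baseline as covariate, the required n stays below 67 over the whole range.

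**Step 4. The baseline window.** Screening, treatment and follow-up add to 2 + 4 + 4 = 10 weeks, the length of the diary. This points to a 2-week pre-treatment diary, but it is an inference. The entry criterion on attack frequency refers to the most recent month and is an eligibility rule, not an outcome baseline.

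**The case against.** The strongest reply is that the outcome wording can mean change from baseline to week 4. On that reading it matches the improvement used for sizing, and nothing is inconsistent. ANCOVA also commonly implies adjustment for the baseline value, and a condensed article may leave units and windows to the full protocol or SAP. Much of this stands: the text is ambiguous, and a mismatch is not proven. What remains is that the article does list its covariates and baseline frequency is absent, and that no sentence links the sized quantity to the analysed one.

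A reader might infer four stronger things that the document does not support:

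- **That the planned difference is wrong for the analysed variable.** It is not; by Step 2, 2.43 applies to both readings.
- **That a 2-week baseline and a 4-week outcome cannot be compared.** No section subtracts raw counts from unequal windows. The entry criterion already expresses attack frequency per week, and on a common rate unequal windows do not bias the comparison.
- **That power must be lower than planned because a short baseline adds noise.** This needs SD 5 to come from equal, longer windows, which is not stated. Over the range of r in Step 3, power can move either way.
- **That the first secondary outcome certainly overlaps the primary.** It does so only if the phrase means a cumulative window. Read as a change to the end of follow-up, it is a durability measure.

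**Conclusion.** The point holds as an ambiguity in the primary outcome that leaves the SD, and hence the power, unverified. The difference of 2.43 and the arithmetic behind 67 per group are sound. If the analysis is of change, power is 80% as planned. If it is of the 4-week frequency without baseline, power at 67 per group lies between about 91% (r = 0.3) and 43% (r = 0.8). The document gives no means of telling where in that range the trial falls. These figures assume that SD 5 is the SD of change, that variances are equal at both times, and that the outcome is near enough to normal.

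Adding baseline as a covariate removes most of this dependence. On the same assumptions power is about 94% to 84%, so the planned size is enough. The point should be corrected, but it does not call for a larger trial.

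**What to change.** 1. Define the primary outcome as attacks per week over treatment weeks 1 to 4: attacks / diary days × 7.
2. Add the attack rate per week from the pre-treatment diary to the ANCOVA covariates, and state its window (2 weeks, if the inference from the 10-week diary is right).
3. State which quantity, unit and window 5.57, 3.14 and 5 refer to. Unit conversion alone does not turn the SD of a change score into an ANCOVA residual SD; that needs the correlation with baseline, or a range for it as in the table above.
4. State that the first secondary outcome is attacks per week over follow-up weeks 5 to 8 only.

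The cost is wording in the protocol and analysis plan, one added covariate, and a return to the source study for the meaning of its SD. No new data are needed, because the diary already covers these periods, and the sample size need not change on the stated assumptions. The article reports 12 patients included, so the definition can be settled and dated well before any unblinded analysis.
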